### 6.3.2 Primary Endpoint: Immune Response

For all immunogenicity endpoints, seroconversion is defined as the proportion of subjects with either a pre-vaccination strain-specific HAI titer  $<1:10$  and a post-vaccination HAI titer  $\geq 1:40$  or a pre-vaccination HAI titer  $\geq 1:40$  and a minimum four-fold rise in post-vaccination HAI antibody titer.

- Seroconversion for each of the 2012/13 influenza vaccine strains at 3 weeks after completion of the HA DNA prime-boost regimens (Group 1 and Group 2), or 3 weeks after the ATIV or TIV prime (Group 3 and Group 4)
- Geometric Mean HAI Titer for each of the 2012/13 influenza vaccine strains at 3 weeks after completion of the HA DNA prime-boost regimens (Group 1 and Group 2), or 3 weeks after the ATIV or TIV prime (Group 3 and Group 4)

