## **1.5 ASSESSMENT OF IMMUNOGENICITY**

In protocol VRC 703, specimens to evaluate immunogenicity will be taken at baseline and at specified time points. The primary immunogenicity timepoint is 3 weeks after the boost. Measurements of antibody, B cell and T cell responses will be assessed. Hemagglutinin (HA)-specific antibody as measured by HAI assay is the traditional benchmark measure of immune response to influenza vaccines and will be conducted on stored samples obtained throughout the study. The HA-specific immune responses will be assessed through 24 weeks after the boost. Because these adult study subjects are likely to have pre-existing immune responses to many influenza hemagglutinin antigens and the effect of vaccination on other humoral and T cell responses is of interest, a variety of exploratory evaluations of immunogenicity may also be performed. HA-specific T cell responses measured by intracellular cytokine staining (ICS) assay or ELISpot, other HA-antibody assays, and assays to evaluate cross-reactivity will be performed at timepoints throughout the study as exploratory evaluations.

The detection of antibody by HAI assay is based on a validated laboratory method. The ICS assay is based upon previously published methods [47] and quantitates the frequency of CD4+ and CD8+ cells that produce interleukin-2, interferon-gamma, or TNF-alpha in response to pools of overlapping peptides representing HA antigens. Specific peptides will also be used to detect T cell responsiveness by an ELISpot assay, modified from a previously published method [48].

Research samples for immunogenicity assays will be processed by the NIAID Vaccine Immune T Cell and Antibody Laboratory (NVITAL) in Gaithersburg, MD, where many of the immunogenicity assays will also be performed. Some immunogenicity assays may be performed by VRC laboratories in Bethesda, MD, approved contract laboratories, or approved research collaborators.

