### 3 STUDY OBJECTIVES

For the study objectives, an HAI response (seroconversion) is defined as  $\geq 1:40$  for baseline-negative subjects or 4-fold greater than baseline for subjects with pre-existing immunity.

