#### 4.2.3 Enrollment Visit

For all groups, enrollment is defined as the day of first study injection and is designated Study Day 0. Pregnancy test results for women of reproductive potential must be confirmed as negative on the day of enrollment prior to the study injection. Day 0 evaluations prior to the first injection are the baseline for subsequent safety and immunogenicity assessments. If any evaluation is not performed on Day 0, then the baseline will be the screening evaluation.

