#### 6.5.4 Analysis of Immune Responses

The primary analysis for immunogenicity will employ the intent-to-treat (ITT) principle, i.e., all data from enrolled subjects will be used, and subjects will be analyzed according to the study regimen to which they were randomized regardless of the product(s) received. If there are cases of a subject receiving a regimen different from the randomized assignment or subjects who did not complete the prime-boost regimen, then per-protocol analysis may also be performed, according to actual study product received and excluding subjects who did not complete the prime-boost regimen.

The frequency of immune response will be analyzed by tabulating the seroconversion (proportion of subjects with either a pre-vaccination strain-specific HAI titer  $<1:10$  and a post-vaccination HAI titer  $\geq 1:40$  or a pre-vaccination HAI titer  $\geq 1:40$  and a minimum four-fold rise in post-vaccination HAI antibody titer) and exact 95% confidence intervals for each study group. The magnitude of immune response will be analyzed by tabulating the geometric mean titer for each study group. The immune response may also be summarized separately for each age

subgroup. Fisher's exact tests will be used to compare seroconversion between any two study groups.

Missing responses will be assumed to be missing at random, i.e., conditional on the observed data the missingness is independent of the unobserved responses, no imputations for missing data will be made.

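### The seroconversion rule in Sections 6.3.2 and 6.5.4 makes every subject with a baseline HAI titer from 1:10 to below 1:40 a non-responder, and it contradicts Section 3

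*Protocol*

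**What the plan says.** Section 6.3.2 of the protocol sets the rule and its scope: "For all immunogenicity endpoints, seroconversion is defined as the proportion of subjects" who satisfy one of two conditions. The first is "with either a pre-vaccination strain-specific HAI titer $<1:10$ and a post-vaccination HAI titer $\geq 1:40". The second is "or a pre-vaccination HAI titer $\geq 1:40$ and a minimum four-fold rise in post-vaccination HAI antibody titer". Section 6.5.4 repeats the same cut-offs for the analysis. The secondary seroconversion endpoint in 6.3.3 uses the same term.

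Section 3 defines the same response for the study objectives in another way: a titer of at least 1:40 "for baseline-negative subjects or 4-fold greater than baseline for subjects with pre-existing immunity". It gives no titer cut-off for being baseline-negative.

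Three other statements bear on the point. Section 4.2.3 fixes the reference titer: "Day 0 evaluations prior to the first injection are the baseline for subsequent safety and immunogenicity assessments", with the screening evaluation as fallback. Section 6.5.4 applies the intent-to-treat principle, under which "all data from enrolled subjects will be used". Section 1.5 describes the population: "Because these adult study subjects are likely to have pre-existing immune responses to many influenza hemagglutinin antigens".

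**The concern.** The two conditions in 6.3.2 do not meet. The first ends just below 1:10 and the second starts at 1:40, so baselines of 1:10 and 1:20 lie between them. No rule in the protocol excludes or reassigns these subjects. The endpoint is a proportion of subjects under intent-to-treat, so they remain in the denominator as failures fixed at baseline.

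Section 3 leaves no such gap. The same subject can therefore be a responder for the primary objective and a non-responder for the endpoint that is meant to measure it. At stake is the primary seroconversion comparison (Group 1 with Group 3, and Group 2 with Group 4, for three strains), together with the secondary seroconversion rates. The affected subjects are not a remote possibility, since the protocol itself expects pre-existing responses.

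**Working it through.** **Classification (no assumption needed).** Applying each rule to baseline and post-vaccination titers on a two-fold scale:

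| Baseline → post | 6.3.2 / 6.5.4 | Section 3, negative = <1:10 | Section 3, negative = <1:40 |
|---|---|---|---|
| <1:10 → 1:40 | yes | yes | yes |
| 1:10 → 1:40 | no | yes | yes |
| 1:20 → 1:40 | no | no | yes |
| 1:20 → 1:80 | no | yes | yes |
| 1:20 → 1:640 | no | yes | yes |
| 1:40 → 1:160 | yes | yes | yes |

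The rules agree below 1:10 and from 1:40 upward, and differ only in the gap. There, a rise of at least four-fold counts under either reading of Section 3 and never under 6.3.2. The two readings of Section 3 differ from each other only for 1:20 → 1:40, so its cut-off also needs stating.

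**Size of the understatement.** Let g be the share of subjects with a baseline from 1:10 to below 1:40 for a strain, and r the response rate in that band under a complete definition. The 6.3.2 rule lowers the observed rate by g × r.

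**The plan's own power figures.** Exact enumeration of the two-sided Fisher test at 5% over two independent binomials reproduces Table 6-3 to within one point in the nine rows run. At N=55, 0.4 versus 0.7 gives 84.6% (table 85), 0.5 versus 0.8 gives 89.1% (89) and 0.7 versus 0.9 gives 68.2% (68). The table's arithmetic is sound.

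**Illustrative effect on power.** Assumptions: g is the same in both groups, response is unrelated to baseline, and Table 6-3 rates are rates under a complete definition. Then observed rate = table rate × (1 − g). For 0.50 versus 0.80, N=55:

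| g | Observed rates | Power |
|---|---|---|
| 0 | 0.50 vs 0.80 | 89.1% |
| 10% | 0.45 vs 0.72 | 76.7% |
| 20% | 0.40 vs 0.64 | 63.5% |
| 30% | 0.35 vs 0.56 | 51.1% |
| 40% | 0.30 vs 0.48 | 41.1% |

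**Illustrative effect on false positives.** Take a true rate of 0.60 in both groups, N=55.

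- No gap subjects: the test rejects 3.0% of the time, the actual size of Fisher's test here.
- Equal shares of 20% (0.48 vs 0.48) or 30% (0.42 vs 0.42): 2.8% and 2.9%, so no inflation.
- Shares of 25% vs 35%: 0.60 × 0.75 = 0.45 and 0.60 × 0.65 = 0.39; rejection 6.3%.
- Shares of 20% vs 40%: 0.60 × 0.80 = 0.48 and 0.60 × 0.60 = 0.36; rejection 18.1%.

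**The case against.** The best defence is that the second cut-off is a slip, 1:40 for 1:10, copied once, and that titers are collected in any case, so correcting it before analysis loses nothing. That is plausible, but it does not remove the point: both statistical sections carry the same text, and anyone programming from them would implement the gap.

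The objections to the consequences carry more weight, and they limit what can be claimed.

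- A reader might infer that the trial's power is well below Table 6-3. The documents do not support that as fact. They give no share by baseline titer, and Section 6.4.3 presents the table over a range of possible seroconversion rates. If those are overall rates under the 6.3.2 rule, the table is unchanged. Section 6.4 also says the study is not designed around a formal superiority or non-inferiority hypothesis.
- A reader might infer an inflated false-positive rate, because each primary contrast crosses two separately enrolled cohorts (Groups 1 and 2 from August 2012, Groups 3 to 6 from October 2012). That requires the underlying low-positive shares to differ between cohorts; equal shares leave the size near 3%. Nothing in the protocol documents such a difference. Both cohorts share the eligibility criteria, including no 2012/13 vaccine before enrolment, and the same age and site stratification. Separate enrolment is its own design question and would touch GMT and a corrected definition too.
- A reader might infer that the whole primary immunogenicity analysis is compromised. It is not. The co-primary GMT endpoint does not use the rule, nor do the secondary GMT and neutralizing-antibody endpoints.

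**Conclusion.** The defect stands as a matter of wording and needs no assumption. Following 6.3.2 and 6.5.4 as written misclassifies responders on a primary endpoint and conflicts with Section 3. It must be corrected before the HAI data are analysed.

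Its numerical size cannot be fixed from the protocol. The understatement is the low-positive share times the response rate in that band, strain by strain, and it is zero for a strain with no such subjects or no responders among them. The fall in power from 89% to between 77% and 41% is an illustration for shares of 10% to 40% under the stated reading of Table 6-3. The 6% and 18% rejection rates apply only if the cohorts truly differ in that share, by 25% vs 35% or 20% vs 40%.

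**What to change.** Use one exhaustive definition, word for word, in Sections 3, 6.3.2 and 6.5.4: a pre-vaccination HAI titer below 1:10 with a post-vaccination titer of at least 1:40, or a pre-vaccination titer of at least 1:10 with at least a four-fold rise. State in Section 3 that baseline-negative means below 1:10. Keep the baseline as Section 4.2.3 already sets it: Day 0 before the first injection, with the screening fallback.

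The cost is a wording change in three sections and the matching analysis code. No new samples, assays or subjects are needed, and Table 6-3 can stand, read as rates under the corrected definition. Make the change before any HAI results by group are analysed, including the early immunogenicity review that Section 6.5.5 allows, so that the choice of definition cannot depend on the outcome.

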### 6.3.3 Secondary Endpoints: Immune Responses

- Seroconversion for each of the 2012/13 and 2013/14 influenza vaccine strains at three weeks after each study injection, for all study groups.
- Geometric Mean HAI Titer for each of the 2012/13 and 2013/14 influenza vaccine strains before vaccination and at 3 weeks after each study injection, for all study groups.
- Proportion of subjects with four-fold rise in 2012/13 and 2013/14 influenza vaccine strain-specific H1, H3, and B neutralizing antibodies before vaccination and at 3 weeks after each study injection, for all study groups.
- Geometric Mean neutralization titer of 2012/13 and 2013/14 influenza vaccine strain-specific H1, H3, and B neutralizing antibodies before vaccination and at 3 weeks after each study injection, for all study groups.

### 6.3.4 Exploratory Endpoints: Immune Responses

- Proportion of subjects with anti-stem antibodies pre-vaccination and at 3 weeks and 24 weeks after the boost vaccination for each schedule.
- Proportion of subjects with positive HA-specific T-cell responses (as measured by ICS assay or ELISpot assay) before each vaccination, 3 weeks after each vaccination and 24 weeks after the boost for all study groups.

Other exploratory assays to evaluate antibody or T cell responses over the time course of the study may also be performed.

## 6.4 **SAMPLE SIZE AND ACCRUAL**

The study is planned to enroll a total of 330 healthy adults stratified by age groups (18-50 and 51-70) to receive one of six vaccine regimens defined in **Table 4-1**. The first 110 subjects enrolled will be randomized with equal allocation to receive 2012/13 HA DNA prime with 2012/13 ATIV boost (Group 1) or 2012/13 HA DNA prime with 2012/13 TIV boost (Group 2). The remaining 220 subjects will be randomized with equal allocation to receive 2012/13 ATIV

with 2013/14 ATIV boost (Group 3), 2012/13 TIV with 2013/14 TIV boost (Group 4), concurrent administration of 2012/13 HA DNA and ATIV with 2013/14 ATIV boost (Group 5), or concurrent administration of 2012/13 HA DNA and TIV with 2013/14 TIV boost (Group 6).

Enrollments may occur rapidly at more than one site. The EMMES Corporation will carefully monitor study enrollment and notify all sites and the VRC Protocol Chair when the completion of enrollment is near in order to end recruitment and to plan how to fairly accommodate, to the degree possible, the enrollment of eligible volunteers that have already been recruited. The decision to stop study enrollments will be made by the VRC Protocol Chair.

This study is not designed to test a formal null hypothesis for superiority or non-inferiority. This section does provide an indication of the power available to observe specific events (e.g., particular adverse events) assuming a range of underlying “true” rates, the precision available in estimating immune response rates, and the power to detect differences in response rates between Study Groups. While drop-out is expected to be low, power calculations assuming approximately 10% drop-out (N=50/per group) are also presented.

#### 6.4.1 Power Calculations for Evaluation of Safety

Sample size calculations for primary safety objectives are expressed in terms of the ability to detect safety or reactogenicity events in each study group (N = 55). The ability of the study to identify safety events will be expressed in terms of the probability of observing a certain number of events. Useful values are the minimum true event rate such that the probability of observing at least one event is at least 90% and the maximum true event rate such that the probability of not observing any event is at least 90%. Within each Study Group of 55 subjects, there is over 90% chance to observe at least 1 event if the true rate is at least 0.05 (1 of 20) and over 90% chance to observe no events if the true rate is less than 0.002 (1 of 500).

Probabilities of not observing any events or observing more than 1 event are presented in **Table 6-1** for a range of possible true event rates. These calculations provide a more complete picture of the sensitivity of this study design to identify potential safety concerns with the vaccine.

**Table 6-1: Probability of Observing Events for Different Safety and Immunogenicity Scenarios within a Study Group (n = 55)**

| True Event Rate     | N=55          |               | N=50          |               |
|---------------------|---------------|---------------|---------------|---------------|
|                     | Pr (0 events) | Pr (>1 event) | Pr (0 events) | Pr (>1 event) |
| 0.003
(1 in 300) | 0.85          | 0.01          | 0.86          | 0.01          |
| 0.01
(1 in 100)  | 0.58          | 0.11          | 0.61          | 0.091         |
| 0.05
(1 in 20)   | 0.06          | 0.77          | 0.08          | 0.72          |
| 0.1
(1 in 10)    | 0             | 0.98          | 0.01          | 0.97          |
| 0.2
(1 in 5)     | 0             | 1             | 0             | 1             |

**Table 6-2** gives the upper and lower bounds for 95% exact (Clopper-Pearson) binomial confidence intervals of the true event rates for a range of possible numbers of observed events. If none of the 55 subjects in a Study Group experience the event of interest, the 95% exact 2-sided upper confidence bound for the event rate is 0.07.

**Table 6-2: 95% Exact Confidence Intervals for the True Rate for a Range of Possible Observed Rates within a Study Group (N=55)**

| Observed Rate | N=55        |             | N=50        |             |
|---------------|-------------|-------------|-------------|-------------|
|               | Lower bound | Upper bound | Lower bound | Upper bound |
| 0             | 0           | 0.07        | 0           | 0.07        |
| 0.10          | 0.04        | 0.21        | 0.03        | 0.22        |
| 0.20          | 0.10        | 0.33        | 0.10        | 0.34        |
| 0.30          | 0.18        | 0.44        | 0.18        | 0.45        |
| 0.40          | 0.27        | 0.54        | 0.26        | 0.55        |
| 0.50          | 0.36        | 0.64        | 0.36        | 0.65        |
| 0.60          | 0.46        | 0.73        | 0.45        | 0.74        |
| 0.70          | 0.56        | 0.82        | 0.55        | 0.82        |
| 0.80          | 0.67        | 0.87        | 0.66        | 0.90        |
| 0.90          | 0.78        | 0.93        | 0.78        | 0.97        |
| 1             | 0.94        | 1.0         | 0.93        | 1.00        |

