#### 6.4.2 Power Calculations for Evaluation of Immune Responses

The tables presented in the previous section for evaluation of safety response, are also applicable to the evaluation of immune response (e.g., seroconversion). **Table 6-1** gives the probabilities of observing no subjects with immune response or at least 2 subjects with immune response over a range of underlying response rates. **Table 6-2** gives the exact 95% confidence intervals over a range of observed response rates for each Study Group.

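### Table 6-2 prints upper exact confidence limits for N=55 that are about 0.03 too low at observed rates 0.80 and 0.90

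*Protocol*

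**What the plan says.** Section 6.4.1 of the protocol states that Table 6-2 "gives the upper and lower bounds for 95% exact (Clopper-Pearson) binomial confidence intervals of the true event rates". The text just before the table treats the limits as two-sided: with no events among 55 subjects, "the 95% exact 2-sided upper confidence bound for the event rate is 0.07". The table has one pair of columns for N=55 and one for N=50, the second because section 6.4 says "power calculations assuming approximately 10% drop-out (N=50/per group) are also presented".

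Reading across as N=55 lower, N=55 upper, N=50 lower, N=50 upper, the two rows at issue after the observed rate are:

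- Rate 0.80: "0.80 | 0.67 | 0.87 | 0.66 | 0.90"
- Rate 0.90: "0.90 | 0.78 | 0.93 | 0.78 | 0.97"

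Section 6.4.2 extends the table to immune response, saying that it "gives the exact 95% confidence intervals over a range of observed response rates for each Study Group".

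**The concern.** Two features of the table look wrong before anything is computed.

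- **N=55 against N=50.** The N=55 upper limits lie 0.03 and 0.04 below the N=50 limits in the same rows. Five more subjects cannot move an exact limit that far.
- **Symmetry.** Clopper-Pearson limits mirror around 0.5, and the printed N=55 limits at 0.80 and 0.90 do not mirror those at 0.20 and 0.10.

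What is at stake is the stated precision for seroconversion, a primary immunogenicity endpoint (section 6.3.2). Section 6.4 says the study is not built around a formal hypothesis test and offers estimation precision as part of its account of the group size. Table 6-3 uses 0.8 and 0.9 as prime-boost seroconversion scenarios, so the errors fall in the range the sponsor planned for. Both errors make the intervals look narrower than they are.

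**Working it through.** **Inputs.** The method is exact Clopper-Pearson, 95%, two-sided (section 6.4.1). Group sizes are n = 55 and n = 50 (section 6.4 and Table 6-2). The count is x = rate × n.

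**Formula.** Lower limit = 0.025 quantile of Beta(x, n − x + 1). Upper limit = 0.975 quantile of Beta(x + 1, n − x).

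**Step 1: reproduce cells that are right.** The N=50 entries in the same two rows come out as printed:

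| Count | Computed | Printed |
|---|---|---|
| 40/50 | 0.6628 to 0.8997 | 0.66 to 0.90 |
| 45/50 | 0.7819 to 0.9667 | 0.78 to 0.97 |

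Every other cell of the table, for both group sizes, reproduces to within 0.01. The formula and the reading of the columns are therefore the sponsor's.

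**Step 2: the two N=55 rows.** 0.80 × 55 = 44 exactly, but 0.90 × 55 = 49.5, so three counts are shown for the second row.

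| Rate | x | Computed | Printed |
|---|---|---|---|
| 0.80 | 44 | 0.6703 to 0.8957 | 0.67 to 0.87 |
| 0.90 | 49 | 0.7775 to 0.9589 | 0.78 to 0.93 |
| 0.90 | 49.5 | 0.7889 to 0.9645 | 0.78 to 0.93 |
| 0.90 | 50 | 0.8005 to 0.9698 | 0.78 to 0.93 |

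The upper limits should be 0.90 and 0.96 to 0.97. The lower limit at 0.80 is right. The lower limit at 0.90 is right for 49/55 and 0.01 low for x = 49.5.

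**Step 3: the table against itself.** If x of n gives (L, U), then n − x of n gives (1 − U, 1 − L).

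- The N=55 part of the 0.20 row, "0.20 | 0.10 | 0.33 | 0.10 | 0.34", is 0.10 to 0.33. Mirrored: 1 − 0.33 = 0.67 and 1 − 0.10 = 0.90. The table prints 0.67 and 0.87.
- The N=55 entry at 0.10 is 0.04 to 0.21. Mirrored: 1 − 0.21 = 0.79 and 1 − 0.04 = 0.96. The table prints 0.78 and 0.93.
- The other N=55 pairs agree as printed: 0.30 (0.18 to 0.44) with 0.70 (0.56 to 0.82), and 0.40 (0.27 to 0.54) with 0.60 (0.46 to 0.73).

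**Step 4: which count the table uses at half-integers.** By the mirror rule and step 2, at rate 0.10 the limits are:

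- x = 5: 0.0302 to 0.1995
- x = 5.5: 0.0355 to 0.2111
- x = 6: 0.0411 to 0.2225

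Only x = 5.5 rounds to the printed 0.04 to 0.21. The same convention at rate 0.90 is x = 49.5, which rounds to 0.79 to 0.96.

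**Step 5: effect of five more subjects.** At 0.80 the upper limit moves by 0.8997 − 0.8957 = 0.0040. At 0.90 it moves by 0.9667 − 0.9645 = 0.0022. The printed gaps are 0.90 − 0.87 = 0.03 and 0.97 − 0.93 = 0.04.

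**Step 6: could another method explain the cells?** Upper limits under alternatives:

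| Method | 44/55 | 49/55 |
|---|---|---|
| One-sided 95% Clopper-Pearson | 0.884 | 0.951 |
| Wald | 0.906 | 0.973 |
| Wilson | 0.884 | 0.949 |
| Jeffreys | 0.889 | 0.953 |

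None gives 0.87 or 0.93, and x = 49.5 or 50 gives higher values still.

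**Step 7: size in width.**

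| Rate (x) | Correct width | Printed width | Understated by |
|---|---|---|---|
| 0.80 (44) | 0.8957 − 0.6703 = 0.225 | 0.87 − 0.67 = 0.20 | 1 − 0.20/0.225 ≈ 11% |
| 0.90 (49) | 0.9589 − 0.7775 = 0.181 | 0.93 − 0.78 = 0.15 | 1 − 0.15/0.181 ≈ 17% |
| 0.90 (49.5) | 0.9645 − 0.7889 = 0.176 | 0.15 | 1 − 0.15/0.176 ≈ 15% |
| 0.90 (50) | 0.9698 − 0.8005 = 0.169 | 0.15 | 1 − 0.15/0.169 ≈ 11% |

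**The case against.** The strongest reply concerns consequence. The table is descriptive. N=55 was not derived from it, and no test, pause rule or decision uses these cells. Tables 6-3 and 6-4 are separate Fisher calculations. Section 6.5.4 has exact intervals computed from the observed data, so the error cannot reach a reported result. All of this stands, and it keeps the point small.

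It is also fair that only upper limits are materially wrong. For a high seroconversion rate, the lower limit shows the smallest response rate the data support, and it is right or within 0.01. The overstated precision is therefore on the upper side only.

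The correct entry at 0.90 does depend on a convention, because 49.5 responders cannot be observed. That leaves the upper limit at 0.96 or 0.97 and shifts the width figure by a few percentage points. It does not rescue 0.93.

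The zero-event bound for N=55 (0.0649, printed as 0.07) is a rounding matter in the conservative direction and is not part of this point.

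**Conclusion.** The concern holds. In Table 6-2, for N=55, the upper limit at rate 0.80 should be 0.90 rather than 0.87, and at rate 0.90 it should be 0.96 (0.97 if 50/55 is meant) rather than 0.93. Each is about 0.03 too low, and the interval widths are understated by roughly 11% to 17%. The result rests only on the method the protocol names (two-sided exact 95%) and on n = 55. The one open choice is the count at rate 0.90, and no choice gives the printed value. This is an error in the stated precision over part of the planning range for seroconversion. It does not affect the design or the planned analysis.

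**What to change.** In the N=55 columns of Table 6-2, print 0.67 to 0.90 at rate 0.80 and 0.79 to 0.96 at rate 0.90. The second entry follows the x = 49.5 convention that the 0.10 row already uses. If real counts are preferred, label the row as 49/55 (0.78 to 0.96) or 50/55 (0.80 to 0.97), and treat the table's other half-integer rows the same way. With the existing convention the cost is two table rows; sample size, power figures and analysis methods do not change.
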